### Oversight and monitoring

#### Data monitoring and quality

Data collection and implementation will be monitored by the research team. Innovations for Poverty Action-Kenya (IPA) will implement all data collection. IPA conducts real-time monitoring of data collection progress to track consent, response rates, refusal reasons and survey duration. During the data collection, IPA also carries out high-frequency data checks to identify potential data problems quickly, such as unexpected missing values. Research assistants and field supervisors also hold weekly debriefings to address any data quality or collection issues in real time. Further details on enumeration team training can be found in online supplemental appendix A.1.3.

The child development assessments will follow data quality guidelines. Supervisors will sit in and observe a subset of child assessments and ensure that all ethical and protocol guidelines are being strictly followed. During the IDELA assessment, there are two questions where children are asked to make drawings or write on paper. Enumerators will photograph their work for a randomly selected 10% sample, which will be reviewed by another staff member to ensure accurate scoring. For anthropometric measurements, data collection will follow the 2019 WHO/UNICEF guidelines,^21^ with details in online supplemental appendix A.1.4. IPA also uses the data quality monitoring checks built into SurveyCTO.

Because this intervention and data collection pose minimal risk, we do not plan external monitoring or formal external auditing.

#### Harms

Because this study comprises data collection with young children alongside a minimal-risk intervention delivered to childcare providers, we do not anticipate any harms, though study participation could disrupt providers’ daily care routines, and children may not want to participate in the assessment. Field staff will prebook assessment sessions to minimise inconvenience to providers, and they will be trained to identify signs that a child is upset or does not assent to participation. IPA will document any adverse events and share them with the PIs. Any serious incidents will be reported promptly to the institutional review boards overseeing this study.

### Participant and public involvement

The participants and/or the public were not involved in the design, conduct, reporting or dissemination plans of this study.

## Statistical analysis

Our primary outcomes are anthropometric indicators (height and weight) of child nutrition and child development indices across cognitive, socioemotional, motor and language domains.

### Primary outcomes

#### Nutritional status

HAZ.Weight-for-age z-scores.Stunting, wasting and underweight.

These will be calculated using WHO growth standards.^24^

#### Child development

Domain-specific scores of IDELA (motor development; emergent literacy; emergent numeracy; socioemotional development) standardised to age-adjusted z-scores using the reference distribution.Composite index of child development created using item response theory.

### Data analysis

First, we will analyse and produce descriptive statistics of the key child development outcomes listed above. Second, we will compare these measurements for children in the treatment communities to those in control communities according to the larger study’s randomised design using multivariable regression. We will include controls for child age, sex and strata (county) fixed effects.

We will also examine these outcomes separately for the C-RCT baseline sample and daycare user sample. Because C-RCT baseline households were identified prior to randomisation and the intervention, we anticipate that differences in outcomes will reflect the causal intention-to-treat impact of improved childcare in the community. For the daycare user sample, we will capture the treatment-on-treated effect, but this could be biased if the quality improvement affected the selection of children into daycares.

We will restrict our child development analysis to children for whom we obtain IDELA data. Furthermore, we restrict our nutritional status analysis to children for whom we obtain valid anthropometric measurements. In the event of missing independent variables, we will code them as zero and include a missing variable flag.

Cross-sectional data gathered concurrently through caregiver and daycare firm surveys will produce a large dataset for measuring the relationship between early child development and nutritional status, as well as whether paid caregiving arrangements are associated with children’s health and development outcomes.

The final report of this study will follow the general CONSORT.

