## Methods: participants, interventions and outcomes

### Study background

The protocol described here builds on an ongoing C-RCT by (1) including a new sample of children enrolled in our study daycares and (2) collecting new data on anthropometric measurements and direct assessments of child development. The existing C-RCT measures the impact of a social franchising model designed to improve childcare quality on firms and families.^10^ We partnered with a Kenya-based social franchising organisation that supports and facilitates the improvement of existing daycare centres through training and continuous mentorship on various areas relevant to running a daycare, including high-quality caregiving practices, health and safety, and business management. The intervention also includes a facility improvement grant and is broad, with components that could improve child health and nutritional status both directly and indirectly. First, the organisation requires and supports improved sanitation practices (eg, installing wash stations, separating toileting from eating locations, etc). Second, it works to improve the physical infrastructure, such as providing rugs for floors. Third, it provides subsidised, fortified porridge for children. These intervention components may directly improve nutritional status and increase cognitive development of children through improved engagement and nutrition.

For the C-RCT, we randomly assigned 25 communities to receive the treatment and 26 to be in the control group, stratifying by county. The research team conducted this randomisation independently after the firm listing, firm baseline and household listing were complete, at which point it shared the assignment with the implementing partner. In treatment communities, the social franchising organisation offered its programme to all existing daycare firms, and it trained and enrolled those interested in its services. The organisation did not enter control communities, allowing us to compare impacts in areas with and without exposure to the franchising model. In this study,^10^ we measure the impact of this social franchising model on childcare quality, provider revenues and parental work outcomes in urban informal settlements across Kenya.

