### Child recruitment

Children born in 2021 or later will be recruited from two sources: (1) households listed in the C-RCT baseline and (2) children currently enrolled in selected daycares. We recruit C-RCT baseline households following the midline survey, after enumerator trust has been built. For the daycare user sample, we ask providers to send study information and consent forms home with parents, and we send enumerators to directly recruit during drop-off times. See detailed recruitment procedures in online supplementalappendix A.1.

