### Data collection

Enumerators will conduct assessments with these two samples of children, measuring height and weight for all children aged 0–5 to measure stunting and wasting and applying the IDELA for children aged 3 and older.^20^ These assessments will be carried out at local daycares (with agreement from daycare owners) and community centres. Measurements of height and weight will follow the 2019 WHO/UNICEF guidelines,^21^ and IDELA will be implemented following the tool guidelines. Details are provided in online supplemental appendix A.1.4 and A.1.5, respectively.

Data collection will be done in two stages, one in October 2025 and one in January 2026. (The two-stage split is because schools in Kenya are generally closed from November to January). Each stage of data collection will be done over 2 days in each community, with two enumerators per day.

All instruments will be programmed into SurveyCTO and administered using tablets. Enumerators will carry manipulatives and other materials as necessary.

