### Consent and assent

We will only collect measures from children for whom we have received informed consent from their caregiver. For children whose households are in the C-RCT survey sample, we will request consent from caregivers to measure and assess their children at the conclusion of the caregiver interview. The child assessment will take place at a separate point in time, and caregivers will be invited to bring the child to that appointment. For the daycare user sample, we will work with daycare owners to obtain informed consent from the caregivers of the children enrolled in their daycare.

Child assent: Once parental consent has been obtained, enumerators will seek child assent before starting the assessment and throughout the process. Assent will be interpreted broadly, with refusal including either verbal or physical hesitancy. If a child becomes very upset, scared or angry, the enumerator will record that the child did not assent and move on to the next child.

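### The intention-to-treat reading of the baseline sample rests on pre-randomisation listing, which protects the listed roster but not the children later assessed

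*Protocol article*

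**What the plan says.** The causal reading of the baseline sample is in Data analysis. The reason comes first, "Because C-RCT baseline households were identified prior to randomisation and the intervention", and the conclusion follows: "we anticipate that differences in outcomes will reflect the causal intention-to-treat impact of improved childcare in the community". Study background confirms the order of events: "The research team conducted this randomisation independently after the firm listing, firm baseline and household listing were complete".

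How a listed child comes to have an outcome is described elsewhere in the article:

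- Child recruitment: "We recruit C-RCT baseline households following the midline survey, after enumerator trust has been built".
- Consent and assent: "we will request consent from caregivers to measure and assess their children at the conclusion of the caregiver interview".
- Consent and assent, on the measurement itself: "The child assessment will take place at a separate point in time, and caregivers will be invited to bring the child to that appointment".
- Data collection: the assessments are "carried out at local daycares (with agreement from daycare owners) and community centres".
- Consent and assent also says that a child who does not assent is passed over.

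Data analysis then fixes who is analysed. The child development analysis keeps only children with IDELA data, and for growth "we restrict our nutritional status analysis to children for whom we obtain valid anthropometric measurements". The missing-data rule stated there covers independent variables only. The same section warns of selection bias for the daycare user sample and gives no such warning for the baseline sample.

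**The concern.** Identifying households before randomisation makes the two arms comparable over everyone on the list. It does not make them comparable over the subset who are found again, agree, turn up and cooperate, because each of those steps happens after communities were assigned. The article reads the result as intention-to-treat on the strength of the first fact, while its analysis rule selects on the second.

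The document's own account makes the question a fair one. The Introduction describes these families as mobile and difficult to reach, so losses between listing and assessment are likely. Some assessments take place in daycares, and daycares are what the intervention changes. If the programme affects whether families stay in the area or keep the appointment, the assessed children could differ between arms in ways related to growth or development. The baseline sample is the contrast that the article presents without a selection caveat, so a reader would lean on it most.

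**Working it through.** **Order of events.** Listing, then randomisation, then midline contact, consent, appointment, assent, and a valid measurement. Only listing precedes randomisation. The stated reason covers the first step, and the analysis set is defined by the last.

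**The plan's yardstick.** Sample size and power calculations gives 1748 control and 1597 treatment children in the baseline sample, and 80% power for 0.14 SD on anthropometry. Study background gives 26 control and 25 treatment communities. The significance level and intra-cluster correlation (ICC) are not in the text shown, so a two-sided 5% level is assumed.

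Detectable effect = (1.960 + 0.842) × √(D_c/1748 + D_t/1597), with D = 1 + (m − 1) × ICC and m = 1748/26 = 67.2 or 1597/25 = 63.9.

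- ICC 0: 2.802 × √(1/1748 + 1/1597) = 0.097 SD.
- ICC 0.0168: D_c = 2.11 and D_t = 2.06, giving 0.14 SD.

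The stated figure is therefore consistent with an ICC of about 0.017. That value is back-solved, so this is not an independent reproduction. The implied standard error is 0.14/2.802 = 0.05 SD.

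**Worst case under differential assessment.** The documents give no participation rates, so those below are assumptions. For a normal outcome with SD 1, let q1 be the share assessed in the arm with more assessed and q0 the share in the other. The share to trim is t = (q1 − q0)/q1. The largest shift in the mean is φ(z₁₋ₜ)/(1 − t).

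| Assessed, q1 v q0 | t | Worst-case shift |
|---|---|---|
| 72% v 70% | 0.028 | 0.07 SD |
| 75% v 70% | 0.067 | 0.14 SD |
| 80% v 70% | 0.125 | 0.24 SD |

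**A milder model.** Suppose assessment follows a probit model whose latent tendency correlates ρ with the outcome. The mean among the assessed is then shifted by ρ × φ(z_q)/q. The factor φ(z_q)/q is 0.497 at q = 70% and 0.424 at q = 75%.

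- Same ρ in both arms, 75% v 70%: the bias is 0.073 × ρ in absolute size, so 0.007 SD at ρ = 0.1 and 0.037 SD at ρ = 0.5.
- Same ρ and equal rates: zero.
- Equal rates of 70%, with ρ = 0 in one arm and 0.2 in the other: 0.497 × 0.2 = 0.10 SD. Equal attendance is therefore not full protection.

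**Effect on the test.** With a standard error of 0.05 SD, a bias of 0.02 SD raises the two-sided 5% error rate to about 7%, 0.04 SD to about 13%, and 0.10 SD to about 52%.

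**The case against.** The strongest reply is that this is ordinary loss of outcome data, which any trial with later measurement faces. The article says only that it anticipates the reading. Children are still compared by the randomised community. The contrast is unbiased if assessment is unrelated to outcome given age, sex and county. If the arm does not change who is assessed, it is unbiased for the children who can be assessed. All of this stands.

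Sensitivity analyses may be in an analysis plan or appendix not shown, so their absence is no fault. The article commits to CONSORT reporting, and the data collection organisation tracks consent, response and refusals, so part of the information needed will exist. The 0.14 SD figure is an extreme case at chosen rates, and its match with the detectable effect follows from that choice.

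A reader might go further and infer that the intention-to-treat property fails, or that venues differ by arm. The documents support neither. They show no difference in participation, name the same venue types without reference to arm, and do not say which sample is assessed where. An independent organisation collects the data, and control-community daycares were also invited to the partner's workshop.

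The reply does not repair the inference itself. The article gives one reason, that reason covers the roster only, and the article also fixes the analysis on the measured subset. This is a stated rule with a stated interpretation, not a detail left for later.

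**Conclusion.** The point holds in a limited form: the intention-to-treat reading of the baseline sample is not secured by the reason given. It rests on an unstated assumption that assessment is non-differential by arm. The article recognises selection for daycare users but not here.

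The size is unknown because participation is not reported. At assumed rates of 75% and 70%, it runs from about 0.01 to 0.04 SD under a common selection mechanism to a worst case of about 0.14 SD. The first range is small against the detectable effect of 0.14 SD, and the second equals it. These figures assume a normal outcome. They show what the plan should be able to rule out and are not an estimate of bias.

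**What to change.** 1. Define the intention-to-treat roster as all children born in 2021 or later in households listed at the C-RCT baseline before randomisation. State how children born into those households after listing are counted.
2. Report and compare by arm, against that roster, the shares reached at midline, consented, attended and assessed, separately for anthropometry and IDELA.
3. Prespecify Lee bounds for use if assessment rates differ by arm. State their monotonicity assumption and that they concern children who would be assessed under either assignment.
4. Prespecify inverse-probability-of-assessment weights as a supporting analysis, using whatever child, household and community data were recorded before randomisation. The article documents only month and year of birth for the child at baseline, so the available predictors should be listed first. This analysis also matters when rates are equal, because equal rates do not rule out different selection.
5. Reword the sentence in Data analysis so that the intention-to-treat reading is conditional on non-differential assessment, with a selection caveat alongside the one for daycare users.

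The cost is a change of wording, logging of participation that is largely collected already, and slightly more analysis. The bounds may make the reported result less precise.

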### Firm recruitment

Within the 51 communities, we conducted a census of all paid daycares, and then a baseline survey with a subset in early 2024, reaching 978 providers. Our implementation partner then invited surveyed firms in treatment and control communities to attend a free half-day child development workshop. We denote the roughly 60% of baseline firms that attended this workshop as the ‘workshop sample’ (see Fitzpatrick *et al*^10^ for more details on their characteristics). In treatment communities, 82.5% of the workshop sample then opted to continue the partner’s programme, undergoing quality improvements and further training. Workshop-attending firms are comparable between treatment and control communities across the range of characteristics we consider, thus allowing us to use the ‘workshop sample’ to compare children in daycares that joined the social franchising organisation in treatment communities with children in daycares that would have likely joined the programme if the implementation partner had entered their community.

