#### Sample size and power calculations

As figure 2 shows, we plan to collect anthropometric measurements from 3345 baseline sample children (1748 control and 1597 treatment) and 660 daycare user sample children (330 control and 330 treatment). This yields 80% statistical power to detect a treatment effect of 0.14 SD on anthropometric measurements for each subsample. For child development, we have 80% power to detect a treatment effect of 0.25 SD, reflecting that roughly 60% of children will be in the relevant age range and that the estimated intra-cluster correlation coefficient is likely to be higher. See online supplemental appendix A.2 for more details. These minimum detectable effect sizes are well within the range of measured impacts found from similar interventions (see Dulal *et al,*^22^ development impacts ranging from 0.30 to 0.52 SD; and see Mamun *et al*,^23^ nutrition impacts averaging 0.20 SD).

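### The daycare-user contrast is labelled treatment-on-treated, but the stated regression does not estimate that effect when 82.5% of treatment workshop daycares continued

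*Protocol article*

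**What the plan says.** Under Data analysis, the protocol article describes one comparison by randomised arm: a multivariable regression of child outcomes in treatment v control communities, with child age, sex and county strata as controls. It is to be run separately in the two samples. The baseline household sample is said to give an intention-to-treat effect. Of the other sample it says: "For the daycare user sample, we will capture the treatment-on-treated effect". The one caveat is that the quality improvement may have changed which children attend.

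Under Firm recruitment, the workshop sample is defined ("We denote the roughly 60% of baseline firms that attended this workshop"), and in treatment communities "82.5% of the workshop sample then opted to continue" with the partner's programme. The same paragraph says the workshop sample makes it possible to "compare children in daycares that joined the social franchising organisation in treatment communities with children in daycares that would have likely joined the programme" had the partner entered their community. The support offered is a balance statement: "Workshop-attending firms are comparable between treatment and control communities across the range of characteristics we consider".

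The Figure 2 caption says that children are recruited from workshop daycares. Subsample analysis and heterogeneity gives the number of selected daycares as 220. Neither says whether the treatment daycares among them are limited to those that joined.

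**The concern.** A treatment-on-treated effect is the effect on children whose daycare took up the programme. A plain contrast by assigned community equals it only if every sampled treatment daycare took up the programme and the control daycares are the right counterfactual for those that did. The article's uptake figure conflicts with the first condition if all workshop daycares are eligible for sampling. If only joiners are sampled, the second condition is unsupported.

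The stated caveat concerns children's entry into daycare. Daycares choosing whether to join is a separate mechanism, and it is not mentioned.

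Measuring causal impact is one of the four study objectives, and this is one of the two samples that address it. As written, the paper could report as TOT either a number that understates the effect of joining or one exposed to differences between daycares that join and those that do not. A reader could not tell which.

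**Working it through.** The plan gives no numerical TOT figure to reproduce, so the check is whether the stated regression yields the labelled quantity.

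**Inputs from the article**
- Uptake among treatment workshop daycares: p = 0.825, so non-uptake is 1 − 0.825 = 0.175 (Firm recruitment).
- The partner did not enter control communities, so non-compliance is one-sided (Study background).
- Baseline firms: 978, of which roughly 60% are in the workshop sample (Firm recruitment). That is 0.60 × 978 ≈ 587 firms, and the 220 selected are 220/587 ≈ 37% of them. A selection step therefore exists, but its rule is not in the article.
- Daycare-user children: 330 per arm (Sample size and power calculations).

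**Notation.** Let τ be the effect in joining daycares. Let J and N be the mean untreated outcomes of children in would-be joining and would-be non-joining daycares.

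**Reading A: the selected daycares include non-joiners**
- Treatment mean = p(J + τ) + (1 − p)N.
- Control mean = pJ + (1 − p)N.
- Difference = pτ = 0.825τ.

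This is an ITT effect among users of workshop daycares. For an illustrative τ = 0.20 SD, the expected contrast is 0.825 × 0.20 = 0.165 SD. About 330 × 0.175 ≈ 58 treatment children would be in non-joining daycares. The calculation assumes that firm uptake among the 220 matches the workshop sample, that children are spread evenly across daycares, and that non-joiners are unaffected. The 82.5% is a share of firms. If the share of children in joining daycares were 0.75 or 0.90 (assumed values), the same τ would appear as 0.15 or 0.18 SD.

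**Reading B: treatment daycares are joiners only, and control daycares are drawn from all workshop attenders**
- Treatment mean = J + τ.
- Control mean = pJ + (1 − p)N.
- Difference = τ + (1 − p)(J − N) = τ + 0.175(J − N).

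The article reports nothing about J − N. For assumed gaps of 0.1, 0.2, 0.3 and 0.5 SD in either direction, the bias would be 0.018, 0.035, 0.053 and 0.088 SD, with the sign of the gap. These figures show the scale only. The balance statement compares all workshop attenders across arms. It does not compare treatment joiners with whichever control daycares are used.

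**Would two-stage least squares recover τ?** Under Reading A, assignment is an instrument for the daycare having joined, with a first stage of about 0.825. The TOT estimate is the ITT estimate divided by 0.825, and its interval is about 1/0.825 = 1.21 times as wide, in proportion to the estimate. Under Reading B, every treatment daycare has joined and no control daycare has. Joining and assignment are then the same variable, so the two-stage estimate is just the plain contrast and corrects nothing.

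**The case against.** The strongest case on the other side has four parts.

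- **Unseen material.** The rule for selecting the 220 daycares, and perhaps a way of picking likely joiners in control communities, may be in the supplementary appendix or in Figure 2. A condensed article may also leave an instrument to the SAP. This stands to the extent that the absence of an instrument is not itself the finding. It does not rescue the sentence in the article, which attaches the TOT label to the regression that the article describes.
- **A warning is given.** The article does not present this estimate as cleanly causal. That is true, but the warning covers child selection and not daycare uptake.
- **Attenuation is conservative.** Under Reading A the error is shrinkage towards zero, and its size rests on firm-level uptake carrying over to children in the selected daycares. Both points stand. A number labelled TOT that understates TOT is still mislabelled.
- **The bias under Reading B is hypothetical.** This stands. Its size and sign depend on a gap that is not reported, so a reader who infers any particular bias, such as 0.05 SD, goes beyond the documents. That all control workshop daycares serve as comparators is also an inference.

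A reader might also infer that the same uptake undermines the power paragraph, where the article says: "These minimum detectable effect sizes are well within the range of measured impacts found from similar interventions". The argument would be that 0.60 × 0.825 = 49.5% of surveyed firms joined, so effects in the baseline sample are roughly halved. The documents do not support this. The baseline effect is correctly labelled ITT. Nothing shows whether the cited impacts are effects on exposed children or are themselves ITT. The 49.5% is a share of firms, not of children, and it assumes that few firms joined without attending the workshop, although the programme was offered to every existing daycare in treatment communities. That argument forms no part of this point.

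**Conclusion.** The TOT label is wrong for the analysis as written. This follows from the article's own uptake figure and its stated regression, and it does not depend on which daycares were sampled. What the contrast estimates instead does depend on that.

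- With non-joiners included, it is ITT among workshop-daycare users, about 0.825 of the effect in joiners under the even-spread and no-effect-on-non-joiners assumptions.
- With joiners only, it is a selected comparison that the reported balance does not cover, at risk of bias whose size and sign the documents do not allow anyone to state.

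The mislabelling is certain. The 0.825 factor is conditional, and no numerical bias is claimed for the joiners-only case. That 17.5% did not join is read from the share that opted to continue.

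**What to change.** State whether the 220 selected daycares include treatment-community daycares that did not join, and how the control daycares were chosen.

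- **If non-joiners are included:** keep them in the analysis. Call the regression contrast the ITT effect among users of workshop daycares. If a TOT effect is wanted, estimate it by two-stage least squares with community assignment as the instrument for the child's daycare having joined, and say that this assumes no effect on children in non-joining daycares. The cost is a change of wording and one further regression, which needs an indicator for each daycare's joining status. Intervals are about 21% wider than for ITT, in proportion to the larger estimate.
- **If only joiners were sampled:** two-stage least squares cannot help. Drop the unqualified TOT label, describe the contrast as joining daycares v selected control workshop daycares, and say that the reported balance does not extend to it. The cost is wording only, with a weaker causal claim.

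In both cases keep the present caveat about child selection. The instrument does not remove it, because assignment may change which children attend as well as what they receive.
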